## Abstract

**Background:**

Heart disease progression occurs in 30% of patients with chronic *Trypanosoma cruzi* infection. Supplementation with selenium (Se) in animal model of *T. cruzi* infection produced promising results. There is evidence that patients with Chagas heart disease have lower Se levels than healthy individuals and patients with *T. cruzi* infection without of cardiac disease. The aim of this investigation is to estimate the effect of Se treatment on prevention of heart disease progression in patients with chagasic cardiopathy.

**Methods:**

The Selenium Treatment and Chagasic Cardiopathy trial is a superiority, double-blind, placebo-controlled, randomized clinical trial. The eligibility criteria are as follows: (1) a Chagas disease diagnosis confirmed by serology; (2) segmental, mild or moderate global left ventricular systolic dysfunction; and (3) age between 18 and 65 years. The exclusion criteria are as follows: (1) pregnancy, (2) diabetes mellitus, (3) tobacco use, (4) alcohol abuse, (5) evidence of nonchagasic heart disease, (6) depression, (7) dysphagia with evidence of food residues in the esophagus, (8) dysphagia with weight loss higher than 15% of usual weight in the last four months and/or (9) conditions that may result in low protocol adherence. The intervention will be 100 μg of sodium selenite once daily for 365 consecutive days compared to placebo. The following are the primary outcomes to be measured: (1) the trajectories of the left ventricular ejection fraction in the follow-up period; (2) reduction of heart disease progression rates, with progression defined as a 10% decrease in left ventricular ejection fraction; and (3) rate of hospital admissions attributable to dysrhythmia, heart failure or stroke due to Chagas disease. One hundred thirty patients will be randomly allocated into either the intervention or placebo group at a ratio of 1:1. The sequence allocation concealment and blinding were planned to be conducted with the strategy of numbered boxes. Both patients and health-care providers will remain blinded to the intervention groups during the 5 years of follow-up.

**Discussion:**

If Se treatment reduces the progression of Chagas cardiopathy, the inclusion of this micronutrient in the daily diet can improve the therapeutic regimen for this neglected tropical disease at low cost.

**Trial registration:**

Clinical Trials.gov ID: NCT00875173 (registered 20 October 20 2008).

## Background

Chagasic cardiopathy is considered the most common and serious manifestation of chronic Chagas disease [1]. This specific form of Chagas disease is associated with high levels of morbidity and mortality [2] and is also a major component in Chagas disease burden [3].

The probability of death among patients with heart failure (HF) attributable to Chagas disease is about 80% over the course of 10 years [4]. According to the Brazilian consensus on Chagas disease [2], patients with *Trypanosoma cruzi* infection and heart disease can be classified into different stages, depending on the electrocardiography (ECG) and echocardiography findings, as follows: stage A (abnormalities on ECG attributable to Chagas disease and no abnormalities detected by echocardiography), stage B1 (abnormal echocardiogram showing ejection fraction (EF) >45% and no HF syndrome), stage B2 (echocardiogram showing EF <45% and no HF), stage C (HF with improvement after treatment optimization) and stage D (HF with no improvement after treatment optimization) [2]. This classification is closely related to prognosis, as left ventricular (LV) function is the strongest predictor of mortality in Chagas heart disease [4–6].

Selenium (Se) is a vital trace element for all organisms, and it has been considered the most important antioxidant mineral, being essential to selenoenzymes such as glutathione-peroxidase (GPx) and others [7]. Se levels vary among the foods of different countries, and a serum level lower than 45 μg/L is considered a potential risk factor for heart disease [8]. The plateau of maximal Se-GPx activity is reached when the plasma Se concentration ranges from 89 to 114 μg/L [8]. Se function is related to its localization in active sites in proteins, as well as to how these proteins, such as GPx, are involved in the protection of biomembranes against the attack of free radicals [9].

Some diseases have been correlated with low serum levels of Se, including AIDS [10], Kashin–Beck disease [11], myxedematous cretinism [12], prostate cancer [13] and cardiopathies [8]. In some cases, low Se levels may be an effect of particular diseases or may contribute to exacerbation of disease progression.

Nutritional Se deficiency or a low Se level is associated with some cardiopathies in animals and humans. There is strong evidence that prolonged Se deficiency in patients receiving home parenteral nutrition is harmful to the heart and can contribute to the development of myocardiopathy [14, 15]. Keshan disease is among the cardiopathies that are classically related to Se deficiency. This condition affects children and young women of childbearing age in areas of China and Eastern Siberia with low soil Se levels [16, 17]. In addition, it is possible that low Se could contribute to the development of AIDS-related myocardiopathy [18]. Similar evidence came from autopsic studies of AIDS patients with heart disease and decreased Se levels [19]. Low Se levels and hyperprolactinemia were reported in patients with peripartum cardiopathy in Africa’s Sahel region, an uncommon form of congestive myocardiopathy that occurs in the last month of pregnancy or in the first 6 months postpartum [20]. Also, Se deficiency may be a contributing factor in congestive HF that affects malnourished children with kwashiorkor disease [21]. There is a positive correlation between Se intake and its blood levels [22], and it has been suggested that Se may play a role in the clinical severity of HF, as evidence indicates that mean Se intake is lower in these patients. Ischemic heart disease has also been linked to low Se levels [23–25].

There is only a single study in which investigators evaluated the relationship between Se levels and chagasic cardiopathy in humans [26]. Nevertheless, there is some consistent evidence showing that low Se levels worsen cardiopathy in Chagas disease animal models [27, 28] and that Se supplementation is beneficial in Chagas disease cardiopathy animal models [29–31]. The mechanisms involved in this effect are modulation of tissue inflammation and oxidative stress [32, 33].

The occasional ingestion of an elevated dose of Se can cause signs of toxicity. Such effects may be seen in association with suicide attempts and accidental ingestion [34]. However, adverse effects seem to be rare and have been reported only in cases of exposure to Se doses over 400 μg/day [14]. Acute symptoms include irritability, pain and trembling; tachycardia; nausea, vomiting and abdominal pain [34–36]; elevated levels of bilirubin and alkaline phosphatase; and altered levels of thyroid hormones [37]. Severe acute and chronic symptoms include pulmonary edema and lesions [36, 38] and garlic breath and diarrhea [34, 35]. Chronic exposure to high Se doses can lead to longer prothrombin time (a marker of hepatic injury); alopecia or dry hair and nails; and convulsions, paralysis and hemiplegia [39–41]. Possible treatments for patients with a diagnosis of acute Se poisoning are gastric wash and induction of vomiting by use of emetics [34]. Monitoring is recommended in mild cases (that is, reactions that do not interfere with activities of daily living), and Se intake may be indefinitely or temporarily interrupted until the symptoms completely disappear in patients with moderate or severe adverse reactions.

### Main objective

Our hypothesis in the present study is that Se supplementation will act as an immune modulator, reducing the inflammation and injures in the heart over time. Our aim is to estimate the effects of Se intake on Chagas heart disease progression, expressed as the decline in left ventricular ejection fraction (LVEF) (Figure 1).

**Figure 1 Fig1:**
[figure not shown]
**Randomization, hypothesis and primary end point.**

### Specific objectives

The following are our specific objectives:To compare the trajectories of LVEF in both intervention groups.To estimate and compare the disease progression incidence rates in both intervention groups.To compare the LVEF average of both intervention groups at the end of the follow-up period.To estimate the effect of Se intake on quality of life.To estimate the Se intake safety level.To follow Se serum levels during the period of Se prescription and possible relation to Se toxicity.To describe nutritional status and Se feeding habits.

## Methods/design

### Ethical considerations

The trial was approved by the Evandro Chagas National Institute of Infectious Diseases (INI) Research Ethics Committee (CEP-INI, CAAE 0043.0.009.000-04) and conforms to standards currently applied by the Brazilian National Committee for Research Ethics (CONEP). An external data safety monitoring board (DSMB) will monitor this trial to guarantee the quality of the study. The trial protocol may be altered, with confirmation from the DSMB, if interim analyses demonstrate statistically significant differences in the primary end point between groups. If significant beneficial effects of Se supplementation are found, Se treatment will be offered to those patients who were randomized to the placebo group.

### Study design and settings

This is a single-center, double-blind, placebo-controlled, superiority randomized clinical trial. Individuals followed at INI will be recruited to participate in the study. INI is a national reference center for treatment and research in infectious diseases and tropical medicine in Brazil. The majority of patients with suspected Chagas disease in Rio de Janeiro State are referred to the INI outpatient unit, either for diagnostic investigation or for specialized health care. At the end of 2012, about 1,100 patients with Chagas disease were followed in an outpatient unit at INI. This unit is able to proceed with more than 100 medical appointments per week for specialized health care for Chagas disease patients. The unit staff is made up of infectious disease specialists, cardiologists, gastroenterologists, nurses, pharmacists and exercise physiologists. Resources such as echocardiography, tomography, 24-hour Holter ECG monitoring, digestive endoscopy and cardiac rehabilitation are also available. Patients receiving health care at this unit are mostly migrants from rural areas who are currently living in the Rio de Janeiro metropolitan area.

### Participants

Patients will be recruited sequentially during their routine outpatient visits. The eligibility criteria are as follows:A confirmed Chagas disease serological diagnosis according to the Brazilian consensus diagnostic investigation recommendation [2].Segmental mild or moderate global left ventricular systolic dysfunction.Age between 18 and 65 years.

The following are the exclusion criteria:Pregnancy or breastfeedingDiabetes mellitusTobacco useAlcohol abuseEvidence of nonchagasic heart diseaseDepressionDysphagia with evidence of food residues in the esophagusDysphagia with weight loss higher than 15% of usual weight in previous four monthsMedical prescription of vitamins or supplementsResidence close to mineral deposits, metal industries or places with radioactive exposureParticipation as a volunteer in other clinical investigations with interventionsConditions that may result in low protocol adherence.

Patients who meet the inclusion criteria will be invited to participate in the study, and a signed written informed consent will be obtained from those patients willing to participate. Participants will undergo an initial interview and baseline blood and urine tests. Initial interviews and tests will include a questionnaire to collect demographic data, medical history, quality of life and detailed information for a nutritional profile including diet *Se* intake, clinical and cardiovascular examinations (ECG and echocardiography) and biochemical and hematological laboratory measurements.

### Intervention

Patients will receive either 100-μg sodium selenite capsules or placebo capsules to be taken orally after a meal once daily for 365 days. The placebo capsules will have the same color, form and texture as those containing Se. At each visit, patients in both groups will receive the number of capsules to be taken until the next scheduled appointment. If, for any reason, treatment interruption is necessary, then the treatment time will be extended until the volunteer takes 365 capsules.

Sodium selenite is not commercialized in isolated form, but is available in combination with other vitamins and supplements. Therefore, a partnership was made with Relthy Technology in Pharmaceutical Services (Indaiatuba, Brazil). That company will be responsible for providing the capsules of sodium selenite and placebo for this investigation.

### Outcomes

There are two main outcomes that will be evaluated. (1) The LVEF will be treated as a continuous measure over time; therefore, the trajectories of both intervention groups will be compared. (2) Disease progression as a main outcome measure will be defined as a 10% decrease in the LVEF, death attributable to Chagas heart disease or hospital admission due to dysrhythmia, stroke or HF attributable to Chagas heart disease.

Four secondary outcomes will be assessed. (1) Disease progression as a secondary outcome measure will be defined as new findings attributable to Chagas heart disease, as compared to the previous tests, based on ECGs (such as intraventricular and atrioventricular node conduction disturbances, electrically inactive areas, T-wave abnormalities, supraventricular and ventricular arrhythmias, bradyarrhythmias, right bundle branch block and left anterior hemiblock or other findings attributable to Chagas disease) or echocardiograms (such as segmental dyskinesia, hypokinesia or akinesia, ventricular aneurysms, global dysfunction or other findings attributable to Chagas disease). (2) Quality of life will be measured with the brief version of the World Health Organization Quality of Life (WHOQOL-Brief) instrument [42]. (3) Reversion rates will be based on comparison of ECG or echocardiogram alterations from previously observations. (4) Adverse events will be recorded.

Volunteers will be evaluated for 5 years after baseline. The outcomes will be blindly assessed every 6 months in the first year. Echocardiography will be conducted every year from the second to fifth years of follow-up. ECG, WHOQOL and other clinical outcomes will be assessed every 6 months from the first to fifth years of follow-up. Follow-up visits to check for adverse events are planned to occur every 3 weeks for the first 2 months, every 2 months for the first year and every 6 months from the second to fifth years of follow-up.

Echocardiographic imaging will be conducted with a Vivid 7 ultrasound system (GE Medical Systems, Milwaukee, WI, USA) equipped with a four-matrix transducer from 2 to 4 MHz. All examination results will be recorded and stored in digital media to allow later analysis at an EchoPAC PC workstation with software version 108.1.12 (GE Medical Systems). The images will be evaluated with the standard left ventricle windows: long and short left parasternal axes (basal, middle and apical) and apical three, four and two chambers. All these images will be recorded with myocardial movements and ECG tracing. Cardiac dimensions will be measured according to the recommendations of the European Society of Echocardiography [43]. LVEF and systolic and diastolic LV final volumes will be estimated according to Simpson’s rule. Segmental analysis will be conducted with the standard 17 segments description. ECGs will be recorded with the standard 12-lead protocol while the patient is at rest. Digital images of the test will be stored in a workstation and printed out on graph paper for later analysis.

Quality of life will be assessed with the WHOQOL-Brief instrument, which was previously validated in a Brazilian population [42]. It is a generic instrument that is easy to understand and apply. It consists of 26 questions in 4 dimensions: physical, psychological, social relationships and environment.

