### Statistical analysis

The type of analysis of major interest is the intention-to-treat analysis. At baseline, both intervention groups will be compared concerning information that might modify disease prognosis to check if random allocation worked properly at that time. The main analysis will be longitudinal modeling of LVEF by comparing the two intervention groups. This modeling will be conducted with marginal models and conditional models. This analytical strategy will also be used for other continuous outcomes, such as the WHOQOL-Brief.

For each binary outcome of interest, incidence rates will be estimated and compared among the different intervention groups, including the adverse events discriminated by severity and causality. Time-dependent survival models will be adjusted for the binary outcomes, as progression may occur more than once for each participant. The survival modeling extension for multiple events of Prentice, Williams and Peterson will be adopted [45].

Secondary analysis will be conducted as per protocol by adjusted regression. This secondary analysis will be conducted mainly if there is an understanding that random allocation did not fulfill its purposes at baseline.

REDCap software [46] will be used for data management, and data analysis will be conducted with R Project software [47].

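### The primary outcomes contradict each other in number and content: three in the abstract, two in Outcomes, with two definitions of progression

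*Protocol article*

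**What the plan says.** All references are to the protocol article.

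- **Abstract, Methods** lists three primary outcomes. It opens with "The following are the primary outcomes to be measured: (1) the trajectories of the left ventricular ejection fraction in the follow-up period". The second is a reduction in progression rates, "with progression defined as a 10% decrease in left ventricular ejection fraction". The third is given as "3) rate of hospital admissions attributable to dysrhythmia, heart failure or stroke due to Chagas disease". Death is not mentioned.
- **Outcomes** states "There are two main outcomes that will be evaluated". The first is LVEF over time. The second is a composite: "Disease progression as a main outcome measure will be defined as a 10% decrease in the LVEF, death attributable to Chagas heart disease", or admission for dysrhythmia, stroke or heart failure due to Chagas heart disease.
- **Main objective** expresses progression as LVEF decline.
- **Statistical analysis** says "The main analysis will be longitudinal modeling of LVEF by comparing the two intervention groups".
- **Ethical considerations** lets the protocol be altered "if interim analyses demonstrate statistically significant differences in the primary end point between groups". The end point is in the singular there and is not identified. The Figure 1 caption also uses the singular.
- **Sample size and Table 1** size the trial on progression only, 54% versus 27% over 5 years, with α 0.05 and β 0.20. The rates are based on LVEF decline in an earlier cohort.
- **Interim analyses and stopping rules** puts an LVEF difference and a progression reduction in one list joined by "or", together with safety criteria, all at 0.01.

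**The concern.** The lists differ in substance, not only in level of detail. Admissions are a primary outcome of their own in one place and a component of a composite in the other. Chagas cardiac death counts in one and is absent from the other. The word progression therefore describes two different events.

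Three things depend on which version governs:

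- **The result.** The number of progressors in each arm changes with the definition.
- **The interim trigger.** A protocol change may follow a significant difference in a primary end point that the article does not identify.
- **The sample size.** The outcome called the main analysis is not the one that was sized. The rates for the sized outcome come from LVEF decline, not from the composite.

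**Working it through.** **1. The two definitions applied to the same patients**

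| Patient | Abstract | Outcomes section |
|---|---|---|
| 10% LVEF decrease, no admission | progressor | progressor |
| Heart failure admission, no 10% LVEF decrease | not a progressor (event under the third outcome) | progressor |
| Chagas cardiac death, no earlier decrease or admission | event under none of the three | progressor |

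Two of the three rows disagree, so no single event definition fits both texts.

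**2. The plan's own sample size**

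Inputs from Sample size and Table 1: p1 = 0.54, p2 = 0.27, α = 0.05 (taken as two-sided), power 80%. The mean proportion is 0.405.

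- √(2 × 0.405 × 0.595) = 0.694 and √(0.54 × 0.46 + 0.27 × 0.73) = 0.667.
- n per arm = (1.960 × 0.694 + 0.842 × 0.667)² / 0.27² = 51, or 102 in total. With continuity correction it is 58 per arm, or 116 in total.

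The stated 65 per arm is not reproduced from the stated inputs. An unstated dropout allowance would explain it: 58 / 0.90 rounds up to 65. That is a separate matter and does not affect this point. The calculation does confirm that only a progression proportion was sized.

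**3. Familywise error if any one outcome could carry success at 0.05 (assumption)**

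Under independence: 1 − 0.95² = 9.75% for two outcomes and 1 − 0.95³ = 14.3% for three. With equally correlated two-sided z-tests (1,000,000 simulated draws; correlations assumed):

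| Correlation | Two outcomes | Three outcomes |
|---|---|---|
| 0 | 9.7% | 14.3% |
| 0.3 | 9.5% | 13.6% |
| 0.5 | 9.1% | 12.5% |
| 0.7 | 8.4% | 10.9% |
| 0.9 | 7.0% | 8.4% |

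The interim looks are not included.

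**4. Power for progression at 65 per arm under the Table 1 rates**

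Power = Φ[(0.27 × √65 − z × 0.694) / 0.667], where 0.27 × √65 = 2.177.

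- α 0.05 (z = 1.960): Φ(1.22) = 88.9%.
- α 0.025, two-way split (z = 2.241): Φ(0.93) = 82.4%.
- α 0.0167, three-way split (z = 2.394): Φ(0.77) = 78.0%.

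These figures assume no dropout and a simple comparison of proportions, not the recurrent-event model planned for binary outcomes.

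**The case against.** - **LVEF is already ranked first.** The main objective and the named main analysis both point to LVEF, so a reader might say that the trial does have one confirmatory test. This stands in part, and it is too strong to say that no such test exists. But the ranking is informal. The Outcomes section gives progression equal standing as a main outcome, and progression is what was sized.
- **Testing levels belong in the analysis plan.** A reader might infer that each outcome is tested at the full 0.05. The article does not say so: 0.05 appears only as a sample-size input. A multiplicity rule could sit in a plan that is not shown, so its absence alone is no finding. The contradiction between the two lists remains, because no plan can follow both.
- **The error figures are ceilings at the upper end.** This stands. A 10% LVEF decrease comes from the same measurements as the trajectory, so independence is implausible. The three-outcome figures apply only if the abstract governs.
- **The LVEF analysis could be called underpowered.** The article does not support this. It gives no LVEF standard deviation or target difference, and a comparison at one time point would not represent the planned longitudinal model. Power for the trajectory cannot be computed from the article.

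**Conclusion.** The concern holds as a contradiction inside the document. The abstract and the Outcomes section disagree on the number of primary outcomes, on whether admissions stand alone, on whether Chagas cardiac death counts, and so on who is a progressor. The mismatch between the main analysis (LVEF trajectory) and the sized outcome (progression, with rates from LVEF decline) is also in the text.

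The possible inflation of false positives is conditional. It is about 7.0% to 9.75% for two outcomes and 8.4% to 14.3% for three, if any one could carry success at 0.05 and for assumed correlations from 0.9 down to 0. These figures show why the choice matters. They are not the trial's stated error rate.

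**What to change.** Align the abstract, Ethical considerations, Outcomes, Sample size with Table 1, Statistical analysis and the stopping rules on one outcome set and one definition of progression. If the composite is kept, report admissions as a component and not as a separate primary outcome. State which definition the 54% and 27% rates refer to, and identify the primary end point that triggers a protocol change.

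Then state how success is decided. Either option fits the document, and the choice is the sponsor's:

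- **Fixed sequence.** LVEF trajectory first at 0.05, with the progression composite tested only if it succeeds. This follows the main objective and the main analysis. The cost is that progression cannot be claimed if LVEF fails.
- **Two primary outcomes under Holm or Bonferroni.** Either can carry success. At 0.025, power for progression falls from 88.9% to 82.4% at 65 per arm, still above the planned 80%, so no extra patients are needed under the Table 1 rates. Keeping all three outcomes would give 78.0% at 0.0167 and would need 68 per arm.

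This needs a protocol amendment, but no new visits or measurements. Recruitment is still open, and the first interim analysis waits until the last volunteer has 6 months of follow-up. The change can therefore be made before any planned look at the data.
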